### Sample size and power calculation

Petrie et al [12] carried out an intervention (34 controls and 31 in the intervention group) with patients post MI which involved the addition of a health psychologist to usual care who focused on a number of psychological factors including beliefs, expectations and behaviour. The results from this study showed that this intervention produced a significant improvement in a certain patient outcome by follow up of about 20% with a standard error of 40%. Based on the information from this study, were the study to be repeated, 85 subjects in each arm would be needed for 90% power for the effect of the intervention on this patient outcome at a two-sided significance level of 0.05. It can be argued that this can be used as the basis for considering the expected improvement for the present study. Buchwald et al [13] reported that the mean percentage of excess weight loss among obese patients offered bariatric surgery was 62%. If the psychological intervention described here improved this weight loss by a further 20% (i.e. to 74%), by the above reasoning, at 0.05 significance 85 patients randomised to each group would give 90% power to demonstrate statistical significance of the intervention. Bands are expected to constitute 20% of all presenting patients. If 90% power is required to find the intervention statistically significant for bands and for bypass, separately, then 85 patients will need to be randomised for each of bands and bypass for each arm of the study. However we hypothesise that bands will be more responsive to the intervention than bypass and hence we will aim for 60 bands and 85 bypass patients in each of the two arms of the study, making a total of 290 patients for the study. Allowing for some attrition and refusals we propose to invite 335 patients to be recruited into the study, ensuring that 180 of these are bands and the remainder bypass. This sample size will enable us to detect a 20% improvement on usual care in the entire sample with power in excess of 90% and will also enable us to carry out some sub group analyses to explore differential effects with 90% power within those patients who receive either a gastric band or a gastric bypass.

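### The invitation split leaves 155 bypass patients, fewer than the 170 to be randomised, so the stated 90% power for bypass cannot hold as written

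*Protocol article*

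**What the plan says.** Everything is in the section on sample size and power calculation of the protocol article.

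- The basic calculation: "85 subjects in each arm would be needed for 90% power", "at a two-sided significance level of 0.05".
- For separate power in each procedure: "85 patients will need to be randomised for each of bands and bypass for each arm of the study".
- Because bands are expected to respond more strongly, the band number is then reduced: "we will aim for 60 bands and 85 bypass patients in each of the two arms of the study, making a total of 290 patients".
- The recruitment quota that follows: "we propose to invite 335 patients to be recruited into the study, ensuring that 180 of these are bands and the remainder bypass". The stated reason for the larger number is refusals and attrition. No rate is given for either.
- The section closes by claiming more than 90% power for the whole sample and 90% power within each of the two procedures.

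**The concern.** Invitations come before refusals and losses, so in each procedure the number invited should exceed the number to be randomised. For bypass it is smaller. The quota asks for many more bands than the design uses and too few bypass patients, so a recruiter who followed it would miss the bypass target before losing anyone.

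This matters for two reasons. First, the whole-sample comparison needs only 85 per arm, or 170 patients, by the plan's own calculation. The increase to 290 is justified only by the wish for adequate power within each procedure, so a quota that breaks the bypass number defeats the reason for the larger trial. Second, bypass is the only procedure kept at the calculated 85 per arm, and it is the larger group at this centre: 70% of operations against 20% for bands, or 70/90 = 78% of primary cases.

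**Working it through.** **Inputs, all from the sample size section:** two-sided significance level 0.05; power 90%; difference 20; spread 40; 60 bands and 85 bypass per arm; 335 invited, of whom 180 bands. The article calls the spread a standard error, but its sample size is reproduced only if 40 is used as a standard deviation. That reading is used throughout.

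**1. Reproduce the plan's figures.** For two means,

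n per arm = 2 × (1.960 + 1.282)² × (40/20)² = 84.1, rounded up to 85.

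This matches the plan. The total also matches: 2 × (60 + 85) = 290.

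**2. Compare invited with required.**

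| Procedure | To be randomised | Invited | Invited minus required | Share that must be retained |
|---|---|---|---|---|
| Band | 2 × 60 = 120 | 180 | +60 | 120/180 = 66.7% |
| Bypass | 2 × 85 = 170 | 335 − 180 = 155 | −15 | 170/155 = 109.7% |
| Total | 290 | 335 | +45 | 290/335 = 86.6% |

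The total looks reasonable, with an allowance of 1 − 290/335 = 13.4%. The split does not: bypass would need a retention above 100%. If 86.6% were retained in both groups, the trial would end with 180 × 0.866 = 156 bands and 155 × 0.866 = 134 bypass. That still adds to 290, but it is not the 120 and 170 that the design calls for.

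**3. Power for bypass under the stated quota.** With the normal approximation,

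power = Φ( (20/40) × √(n/2) − 1.960 ).

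- Check at n = 85: 0.5 × √42.5 = 3.260, less 1.960 = 1.300, so power = 90.3%.
- At n = 155/2 = 77.5: 0.5 × √38.75 = 3.112, less 1.960 = 1.152, so power = 87.5%.

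The article states no loss rate, so a range is shown. Only the first row needs no assumption about loss.

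| Loss among bypass invitees | Bypass per arm | Power |
|---|---|---|
| none | 77.5 | 87.5% |
| 5% (assumed) | 73.6 | 85.9% |
| 10% (assumed) | 69.8 | 84.0% |
| 13.4% (implied overall by 290/335) | 67.1 | 82.5% |
| 20% (assumed) | 62.0 | 79.5% |

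The t-distribution gives slightly lower values: 90.0% at 85 per arm, 87.1% at 77.5 and 81.9% at 67.

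**4. Whole sample.** At 145 per arm the same formula gives 98.9%, so the claim of more than 90% power overall stands.

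**The case against.** Several points can be made on the other side.

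- *The quota is not a ceiling.* The article only proposes to invite 335, its target remains 85 bypass per arm, and its randomisation section offers information to every eligible patient. About 70% of 500, or 350, bypass operations a year would be enough to reach 170. This shows that the target is attainable at the centre, but not under the stated quota. A general statement about information sheets does not override an explicit instruction on how the 335 are to be divided.
- *It may be a slip.* With the labels exchanged (180 bypass, 155 bands) both targets would be covered, with margins of 1 − 170/180 = 5.6% and 1 − 120/155 = 22.6%. That is plausible, but nothing in the article says so, and only the sponsor can confirm it. A slip in a recruitment quota still has to be corrected.
- *The certain loss is small.* This stands. Without any refusals or attrition, power falls by about three points, and the whole-sample claim is intact. The larger fall depends on an assumed loss rate. However, the sentence that sets the quota itself expects some loss, so the no-loss figure is a best case.
- *The power figures depend on reading 40 as a standard deviation.* True, but that reading is the one that yields the plan's 85. The shortfall of 15 patients does not depend on it.

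**Conclusion.** The concern holds. The number of bypass patients to be invited (155) is below the number to be randomised (170), a shortfall of 15/170 = 8.8% before any loss, and nothing else in the article repairs it. This is arithmetic on the plan's own numbers and needs no outside figure.

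The claim of 90% power within bypass is therefore false under the stated quota. On the plan's standardised effect of 0.5, power is at best about 87%. It is about 82% if the overall 13.4% allowance applies equally to bypass, and between 79.5% and 85.9% for assumed losses of 20% down to 5%. The damage is confined to the analysis by procedure, but that analysis is the stated reason for enlarging the trial to 290. The quota must be corrected.

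**What to change.** The sponsor should first say which figure was intended, then restate the split so that invitations exceed the target in both procedures.

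Keeping 335 invitations and the plan's own overall allowance, the split in proportion to the targets is:

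- bands: 335 × 120/290 = 138.6, about 139;
- bypass: 335 × 170/290 = 196.4, about 196.

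With 86.6% retained these yield 120.3 bands and 169.7 bypass, which is the target to within rounding. Rounding both invitation numbers up would give 139 and 197, one more than 335.

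The band number should also be checked against supply. The participants section implies about 20% of 500, or 100, band operations a year, and recruitment lasts 12 months. That is below 139, and further below the 180 now stated. If the band number is cut to what the centre can provide, the freed invitations should go to bypass.

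Power should then be restated for each procedure from the corrected numbers. For bands, 60 per arm gives 78.2% at the same effect. It reaches 90% only for a difference of about 40 × (1.960 + 1.282) × √(2/60) = 23.7, so the larger effect expected in bands should be written down as a number.

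The cost is one reworded sentence and a changed recruitment quota. The total of 335 need not rise.

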## Background

Obesity is caused by people consuming more energy than they expend and is associated with reduced life expectancy and many serious conditions including heart disease, stroke, diabetes, cancer, gallstones, fatty liver disease and sleep apnoea [1]. Currently almost two-thirds of UK adults are either overweight or obese with overall costs to society forecast to reach £50 billion per year by 2050 on current trends [2].

Although the most common form of management emphasizes changes in diet and exercise, research indicates that weight loss surgery (wls) is the most effective intervention for weight loss for those whose BMI is greater than 40 (or 35 for those with significant health problems) [3]. A systematic review of wls [4] concluded that the mean percentage excess weight loss (EWL) for the Roux-en-Y gastric bypass was 67% and for the gastric band was 42% at one year. WLS has also been shown to result in improvements in a number of other patient outcomes including quality of life, mood, subjective health status and perceptions of eating control [5,6]. Weight loss outcomes are not consistent for all patients and a large minority of patients either do not show the desired loss of excess weight or regain weight by follow up.

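### The 90% power claimed within gastric band patients is unsupported: the plan's own inputs give about 78% at 60 per arm, and within-procedure power is not power to compare procedures

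*Protocol article*

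**What the plan says.** All of this is in the protocol article, under Sample size and power calculation.

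- The inputs come from a psychological intervention trial after myocardial infarction, which found an "improvement in a certain patient outcome by follow up of about 20% with a standard error of 40" per cent. From these, "85 subjects in each arm would be needed for 90% power", "at a two-sided significance level of 0.05".
- The same reasoning is carried over to excess weight loss, as a relative gain of 20% from 62% to 74%.
- For 90% power in bands and bypass separately, "then 85 patients will need to be randomised for each of bands and bypass for each arm of the study".
- The plan then departs from this: "we hypothesise that bands will be more responsive to the intervention than bypass and hence we will aim for 60 bands". That figure is per arm; the bypass target stays at 85 per arm, which makes 290 in total.
- To allow for attrition and refusals, 335 patients are to be invited, 180 of them bands and the rest bypass.
- The section closes by claiming more than 90% power for a 20% improvement in the whole sample, and the ability to "explore differential effects with 90% power within those patients who receive either a gastric band or a gastric bypass".

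**The concern.** The section sets a requirement of 85 per arm in each procedure, plans 60 for one of them, and still claims the power that 85 would give. The only link between these statements is an expectation that bands respond better, with no effect size, standard deviation or source. A reader cannot tell what band effect the 90% refers to.

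The closing phrase adds a second difficulty. A differential effect is a difference between two treatment effects, and power within each procedure says nothing about power to detect that difference. Since the authors themselves expect bands to respond better, readers will look for the contrast.

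Two misreadings are at stake. A non-significant band result could be taken as evidence of no effect from a test believed to have 90% power. A significant result in one procedure and not in the other could be taken as evidence that the procedures differ.

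**Working it through.** **Inputs from the sample size section.** Two-sided alpha 0.05 (z = 1.960); power 90% (z = 1.2816; sum 3.2415); difference 20; spread 40; planned numbers per arm 60 band and 85 bypass; 335 invited, 180 of them bands. The spread is called a standard error, but 85 per arm is reproduced only if it is used as a standard deviation, so d = 20/40 = 0.5.

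**1. The plan's own figure.** n per arm = 2 × 3.2415² / 0.5² = 84.06, rounded up to 85. Power at 85 is Φ(0.5 × √(85/2) − 1.960) = Φ(1.300) = 90.3% (t-test 90.0%). The base figure and the bypass figure at 85 per arm both reproduce.

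**2. Bands at 60 per arm, same effect.** Φ(0.5 × √(60/2) − 1.960) = Φ(0.779) = 78.2% (t-test 77.5%). The 90% does not reproduce.

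**3. Effect needed for 90% at 60 per arm.** d = 3.2415 × √(2/60) = 0.592, and 0.592 × 40 = 23.7 (t-test: 0.597, or 23.9). This is an improvement of about 24% in place of 20%.

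**4. Whole sample, 145 per arm.** Φ(0.5 × √(145/2) − 1.960) = Φ(2.297) = 98.9%. The pooled claim holds.

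**5. Band versus bypass.** The standard error of the difference between the two treatment effects is √(2/60 + 2/85) = 0.238 SD. For 90% power the effects must differ by 3.2415 × 0.238 = 0.77 SD, or about 31 points on the 20/40 scale. Power at smaller differences:

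| Difference between effects (20/40 scale) | In SD | Power |
|---|---|---|
| about 4 (23.7 − 20) | 0.092 | 7% |
| 10 | 0.25 | 18% |
| 20 | 0.50 | 55% |
| 31 | 0.77 | 90% |

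The first row is the band advantage that would just justify 60 rather than 85 per arm.

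**6. Disagreement between procedures.** If both true effects are 20%, the chance that exactly one procedure reaches significance is 0.775 × 0.10 + 0.90 × 0.225 = 28%.

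**7. Invited numbers.** 335 − 180 = 155 bypass patients, against a target of 2 × 85 = 170. Even if all 155 were randomised and followed, that is 77.5 per arm: Φ(0.5 × √(77.5/2) − 1.960) = 87.5%. Bands are over-invited by comparison, 180 for a target of 120. If all 180 were randomised, 90 per arm would give 91.8%.

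**The case against.** **The 90% for bands is not shown to be false.** The section gives a reason for 60 per arm, and its closing 20% is attached to the whole sample. The subgroup claim carries no effect size. A band effect of about 24%, modestly larger and in the hypothesised direction, would give 90%. This stands: the defect is an unstated and unjustified assumption, not a demonstrable miscalculation.

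**The sentence claims power within each procedure, not for an interaction.** This also stands. A reader might infer that the authors claim 90% power for band versus bypass, or that the trial has almost no power for it. The text makes no such claim and names no interaction test, and the power depends on a difference that the document does not state. What remains is that the wording invites the wrong reading, and that power falls well short of 90% even at a 20-point difference.

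**Conflicting results are not the expected outcome.** A reader might infer that significance in one procedure only is what the unequal numbers will produce. At a common 20% effect the chance is about 28%; both procedures are significant about 70% of the time (0.775 × 0.90).

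**The lower band baseline does not settle the matter.** The Background reports that mean excess weight loss "for the gastric band was 42% at one year". A 20% relative gain on that is 8.4 points. With an assumed standard deviation of 24.8 (40% of 62), d is 8.4/24.8 = 0.34 and power about 45%. If the standard deviation scales with the mean to 16.8 (40% of 42), d is 0.5 and power is again 78%. The document gives no standard deviation for excess weight loss, and the 42% comes from a different review from the 62% used for sizing, so the lower figure should carry no weight.

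**Inviting 180 bands might seem to restore the 90%.** The surplus is there for attrition and refusals, no rate is given, and the stated target remains 60 per arm.

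**Conclusion.** The point holds in a limited form and should be fixed. At the only quantified effect, the band subgroup has about 78% power rather than 90%. Reaching 90% needs an improvement of about 24%, which the protocol neither states nor justifies. The 90% should not be attached to differential effects: at the planned numbers that would need effects about 0.77 SD apart. Separately, the invited numbers cannot deliver the bypass target and cap bypass power at about 87.5% before any losses.

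The main comparison is unaffected, at about 99% with 145 per arm, so the defect is confined to the subgroup claims. All figures assume that the 40% is a standard deviation and that d = 0.5 carries over to excess weight loss, where a 12-point gain would imply a standard deviation of 24 points. The section gives no standard deviation for that outcome.

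**What to change.** 1. Replace the subgroup power statement with wording such as: *60 band patients per arm give about 78% power for a 20% improvement (90% for about 24%)*. Alternatively, state the larger band effect assumed and give its justification.
2. Remove the 90% from the phrase on differential effects. Assess any band-versus-bypass difference by one treatment-by-procedure interaction term in the pooled model, reported with its confidence interval and labelled exploratory.
3. Reconcile the invited numbers (180 band, 155 bypass) with the targets (120 band, 170 bypass). Until that is done, 90% power for bypass should not be restated without the condition that 170 bypass patients are randomised.

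The first two changes cost some wording and one model term, and the stated band power becomes less favourable. The third costs either a revised invitation split or total, or a lower stated bypass power.

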### Procedure

Patients attend the bariatric clinic for a multidisciplinary assessment day where they are told if they will be getting the surgery. If they are accepted for surgery they are given an information sheet concerning the present study. Two weeks prior to their operation patients will attend the bariatric clinic for a preoperative appointment where they will have routine tests. At this appointment patients will see the researcher who will explain the trial, obtain informed consent and randomly allocate the patient to either the usual care condition (control group) or the bariatric rehabilitation service (BRS) condition (intervention group). Patients will then complete the baseline questionnaire and either see the health psychologist or not depending on to which condition they are allocated. All patients, from both groups, will complete follow up questionnaires at 3, 6 and 12 months.

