## Methods/Design

### Study design

The study will involve a trial (open randomised parallel group control trial) with patients allocated to receive either usual care or the bariatric rehabilitation service (BRS) pre and post bariatric (obesity) surgery. Follow up measures will be recorded at 3, 6 and 12 months post-surgery at routine follow-up clinics or by post. In addition, qualitative interviews will be carried out with 20 participants from both arms of the trial (BRS n = 10; usual care n = 10). This study received a favourable ethical opinion from the Kent Research Ethics Committee, National Research Ethics Service.

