### Randomisation

All patients who fulfil the inclusion criteria will be given an information sheet. They will be given several weeks to read the information and then they will be approached by the researcher, asked if they have any questions regarding the information sheet and if interested offered a written consent form. Once a patient has consented the researcher will reference the third party blinded randomization, which will be provided by the clinical trial unit at Surrey University, to indicate whether they are allocated to either the BRS or usual care.

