### Intervention group

Those allocated to the BRS (intervention group) will receive usual care as described above plus three 50 minute sessions with a health psychologist pre-operatively (2 weeks prior to surgery), post-operatively (before they are discharged from hospital) and at 3 months follow up. The design of the BRS will be based on the preparation procedures for surgery and cardiac rehabilitation services but will be tailored to the needs of bariatric patients in line with qualitative research carried out by the current author (7; 8). In addition, the BRS has been designed in line with ongoing input from users of two active support groups who have highlighted the need for increased psychological input. The health psychologist will use both didactic methods such as information giving and non didactic methods such as active listening, asking open questions and encouraging reflection. The sessions are fully structured but are flexible to work with the individual patient. In particular the service will address 5 key factors as follows: i) knowledge (ie information about dietary change); ii) beliefs (concerning the causes and solutions to obesity); iii) behaviours (with a focus on diet and physical activity); iv) coping strategies (i.e. managing emotions without using food; identifying alternative and healthy methods of coping; managing other addictions); v) adjustment (i.e. exploring ways to work with the restriction imposed by the operation).

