### Primary outcome measures

Patients' weight and BMI will be obtained in the clinic to provide the primary endpoint measure of the trial. This will be collected preoperatively a couple of weeks before surgery and postoperatively at 3, 6 and 12 months follow up.

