### Secondary outcome measures

Baseline measures of age, sex, weight, height, educational level, and ethnicity will be taken. Patients will also be asked to complete a number of validated measures that have been used previously to assess the impact of bariatric surgery at baseline, 3, 6 and 12 months follow up to evaluate the secondary outcome measures of quality of life, mood, coping and emotional eating (i.e. ADL section of SF-36, [14], profiles of mood states, [15], COPE [16] and DEBQ, [17]).

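### In this open trial the baseline questionnaire comes after allocation, so baseline scores for the self-reported secondary outcomes can reflect knowledge of the arm

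*Protocol article*

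**What the plan says.** All references are to the protocol article.

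- **Study design** describes an "open randomised parallel group control trial".
- **Randomisation** makes consent the only trigger for allocation: "Once a patient has consented the researcher will reference the third party blinded randomization". It does not require a completed baseline first.
- **Procedure** gives the sequence at the appointment two weeks before surgery. The researcher explains the trial and will "obtain informed consent and randomly allocate the patient to either the usual care condition (control group" or, as the sentence goes on, to the BRS. The next sentence reads: "Patients will then complete the baseline questionnaire and either see the health psychologist or not depending on to which condition they are allocated".
- **Secondary outcome measures** says what the questionnaires are for: the "secondary outcome measures of quality of life, mood, coping and emotional eating", recorded at baseline and at 3, 6 and 12 months.
- **Primary outcome measures** takes the primary endpoint from a different source: "Patients' weight and BMI will be obtained in the clinic to provide the primary endpoint measure of the trial".

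**The concern.** A baseline is useful in a randomised comparison because allocation cannot have influenced it. Here the written order gives up that guarantee for every questionnaire measure.

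The allocation is also unlikely to be neutral news. The Background reports that patients with less successful surgery felt unsupported and that their psychological needs went unaddressed. The Intervention group section says service users asked for more psychological input. A patient who has just been given or denied that input may answer mood and coping items differently a few minutes later.

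The article predicts changes in psychological variables, so analysing change from baseline, or adjusting for baseline, would be natural. Either would carry a baseline shift caused by the allocation into the estimated treatment effect. No later analysis can recover the score the patient would have given before allocation.

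**Working it through.** **1. The order.** Procedure puts allocation before the questionnaire, linked by the word *then*. Randomisation agrees, because the allocation is looked up once consent is given. No section puts the questionnaire first or withholds the allocation until it is finished. The third-party randomisation concerns how the allocation is generated and concealed beforehand. It does not keep the patient unaware of the arm afterwards in an open trial.

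**2. The plan's own figure.** The article gives no figure on this point. Its sample size is context only: "85 subjects in each arm would be needed for 90% power for the effect of the intervention on this patient outcome". It reproduces if the stated 40% is read as a standard deviation: 2 x (1.960 + 1.282)² x (40/20)² = 84.1, rounded up to 85, with power 0.903. Re-ordering the visit does not change it.

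**3. Bias formulas.** Score the outcome so that higher is better. Let delta be the BRS-minus-control difference at baseline, in SD units, that is caused only by knowing the allocation. Assume the reaction affects the baseline report and does not carry over to follow-up. Let beta be the within-arm slope of follow-up on baseline, which equals their correlation when the SDs are equal.

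- Change score: bias = -delta
- ANCOVA: bias = -beta x delta
- Follow-up scores compared without the baseline: no bias from this source

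**4. Direction.** Relief in BRS patients or disappointment in controls makes delta positive, so a BRS benefit is understated. Fuller disclosure of problems by BRS patients about to see a psychologist makes delta negative, so a benefit is overstated.

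**5. Size.** The documents give neither delta nor beta. The ranges below are assumed: delta 0.1 to 0.3 SD in absolute value, beta 0.3 to 0.7. To show what such a bias does to a test at two-sided 5% with no true effect, take the planned 60 + 85 = 145 patients per arm and equal SDs:

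- SE(change) = √[2(1 - beta) x 2/145]
- SE(ANCOVA) = √[(1 - beta²) x 2/145]
- Type I error = Φ(|bias|/SE - 1.96) + Φ(-|bias|/SE - 1.96)

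Worked case, delta 0.2 and beta 0.5:

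- Change score: SE 0.117, bias/SE = 0.2/0.117 = 1.70, type I error 0.40.
- ANCOVA: bias 0.10, SE 0.102, bias/SE = 0.98, type I error 0.17.

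| Assumed delta (SD) | Change-score bias (SD) | Type I error, change | ANCOVA bias (SD) | Type I error, ANCOVA |
|---|---|---|---|---|
| 0.1 | 0.1 | 0.11 to 0.20 | 0.03 to 0.07 | 0.06 to 0.13 |
| 0.2 | 0.2 | 0.30 to 0.59 | 0.06 to 0.14 | 0.08 to 0.39 |
| 0.3 | 0.3 | 0.58 to 0.91 | 0.09 to 0.21 | 0.13 to 0.71 |

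Ranges run from beta 0.3 to beta 0.7; biases are absolute values. The table illustrates the mechanism and does not estimate what will happen in this trial.

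**6. Cost of ignoring the baseline.** Relative to ANCOVA, leaving the baseline out multiplies the variance by 1/(1 - beta²): 1/0.91 = 1.10 at beta 0.3 and 1/0.51 = 1.96 at beta 0.7. Avoiding the bias that way gives up the precision the baseline could provide.

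**The case against.** The strongest case on the other side has four parts.

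- **Disclosure is inferred.** The article never says that the patient is told the arm before filling in the form. This is correct. Disclosure is the likeliest reading, given an open design and allocation by the researcher at the same visit, but it supports only the statement that patients *can* know their arm.
- **The questionnaire still precedes treatment.** It is listed before the first psychologist session. This also stands: the exposure is to knowledge of the arm, not clearly to the intervention.
- **The bias needs an analysis that uses the baseline.** The article names no model, and the analysis plan is not shown. This stands as a condition, and the bias is stated on that condition.
- **A condensed article may omit visit details.** That does not answer the point, because the order is written down in Procedure and Randomisation agrees with it.

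A reader might also infer more than the documents support:

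- *That the primary result is compromised.* Weight and BMI are obtained in the clinic, so they are largely unaffected by how a patient feels about the allocation.
- *That the same fault recurs at 3 months*, because the last session is given "post-operatively (before they are discharged from hospital) and at 3 months follow up", when a questionnaire is also due. No baseline is involved there, patients in an open trial would know their arm by then anyway, and Study design allows follow-up by post. The order of steps at that visit is a detail an article may leave out.
- *That the bias is a sizeable share of the planned 0.5 SD effect* (20%/40%). That ratio was carried over to excess weight loss. Nothing in the article is sized on mood, coping, quality of life or emotional eating.
- *That patients unhappy with their arm would decline the questionnaire.* Nothing in the documents supports this.

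**Conclusion.** The point holds as a should-fix on the self-reported secondary outcomes. The stated order lets knowledge of the arm reach the baseline of quality of life, mood, coping and emotional eating.

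The conclusion rests on three conditions: patients learn their arm before completing the form, they react to it in their answers, and the baseline is used for change scores or adjustment. The first is likely from the text, the second is plausible, and the third is left open by the article. Under the assumed ranges the bias is 0.1 to 0.3 SD with change scores and 0.03 to 0.21 SD with ANCOVA. Its sign cannot be settled in advance. The documents do not support a must-fix grade, because only secondary outcomes are exposed.

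**What to change.** In Randomisation and Procedure, state this order for the pre-operative visit:

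1. Consent.
2. Baseline questionnaire completed and handed in.
3. Allocation obtained from the trials unit.
4. Session 1 for patients allocated to the BRS.

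In Randomisation, make the handed-in questionnaire, as well as consent, a condition for looking up the allocation. If the site already works in this order, correct Procedure to say so.

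The steps stay within a visit that already takes place. Sample size, measures and follow-up do not change, and the added cost is essentially nil.
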